#### 2.4.4. Dissemination

Due to the fact that the research project is part of a cumulative doctorate, several publications, lectures and poster presentations are planned. Participants in the study will be informed about publications. Content will be made available in plain language (e.g., through ‘Lay Abstracts’).

#### 2.4.5. Criteria for Success

The criteria for success of ‘phase two’ are defined as follows:Significant improvement in SAQOL-39 score with a medium effect size from pre- to post-intervention.Improvements in SAQOL-39 score between t0 and t1 are significantly greater in the therapy group than in the waiting group.In the semistructured interviews, the participants report generally positive perceptions about the acceptability of the intervention.The fidelity rate is at least 80% in the random sample evaluated by independent rater.Stable values or improvements on the MADRS.Stable values or improvements on the VAS.

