#### 2.3.4. Randomisation

The division of the participants into groups is necessary for conducting the efficacy study and will be carried out as a random allocation by the deputy study director ([name]) [46]. Since the therapy groups will consist of six participants, four blocks must be formed (N = 24). A permutation of the four blocks will be drawn at random, with the first half (*n* = 12) of the permutation being assigned to the therapy group and the second half (*n* = 12) assigned to the waiting group (see Figure 4). Each allocation thus applies to six consecutive participants. Groups will be randomised without balancing.

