#### 2.3.5. Sample Size Justification

It can be assumed that the effects in persons with PPA are comparable to the effect sizes in persons with aphasia after stroke, as the impairment patterns are similar [42], and many approaches for the treatment of poststroke aphasia are successfully transferable to PPA [6,47]. Based on the results of Corsten et al. (2015), who reported an 85.19% improvement in Complaints and an 88.89% improvement in Burden score on the Aachen Life Quality Inventory [23] from baseline to follow-up, with an overall low to moderate effect size (d = 0.22 to 0.58) [19], an a priori power analysis was conducted using G*Power 3.1.7. This resulted in a total sample size of 24 for an estimated effect size of f = 0.275 (d = 0.55; α = 0.05; power = 0.8). It is assumed that with this sample size, effects can be detected in persons with PPA who are examined with the Stroke and Aphasia Quality of Life Scale-39 (SAQOL-39, [48]). It is possible that the effect sizes in persons with PPA are even greater if persons with mild depression are included; thus, a lower baseline score for QoL can be expected.

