## 3. Discussion

To the best of our knowledge, this is the first study including a randomised controlled trial design using a biographic-narrative approach in persons with PPA. Although reminiscence interventions have been used successfully for the treatment of dementia in general [66], only one case study known to us has mentioned the use of the biographic-narrative approach narraktiv in a person with PPA, and the effects were not described [32]. The planned sample size of 24 participants in the present study is also special for a rare disease.

The limitations of this study include the fact that the primary outcome of the study, QoL, is not well defined and is difficult to measure in persons with PPA. Formal assessments that have been used with PPA, such as the Aphasia Impact Questionnaire 21 [16,67], have not yet been translated into or validated in the German language. Thus, the SAQOL-39 will be used, an instrument that is internationally recognised and counted among the core outcome sets [49]. However, the use of an assessment that is standardised for persons with poststroke aphasia and therefore contains items that are not directly related to the symptoms of PPA (e.g., items about mobility) remains a limitation of our study that has arisen due to the lack of German-language versions of measures tailored for persons with PPA [7]. To counteract this limitation, our study additionally utilises semi-structured interviews as qualitative assessments with the aim of gaining additional insights into the impact of our intervention. Influencing and disorder-specific factors should be identified and explored.

It is important to note that the expected improvements in QoL and mood are only potential outcomes. However, there are also challenges that could occur during intervention, e.g., it is possible that cognitive deficits impair storytelling and that the stimulation of lost memories can lead to feelings of frustration [26]. While narraktiv generates improvements in the QoL of persons with chronic aphasia, we must consider that persons with a progressive disease will be targeted in our study. By decreasing awareness of deficits in the course of PPA, it is conceivable that an improvement in QoL may not (only) be due to the intervention. Due to these circumstances, communicative–pragmatic and cognitive functions will be assessed.

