**Figure 4 brainsci-14-00692-f004:**
[figure not shown]
Procedure of ‘phase two’ containing four test points (t0, t1, t2, t3).

**Table 1 brainsci-14-00692-t001:** Measuring instruments, aim and time of measurement.

Measuring Instruments	Aim of Measuring	Time of Measuring
Questionnaires (filled out by participants)		
39-Item Version of the Stroke and Aphasia Quality of Life Scale (SAQOL-39, [48,57])	quality of life	t0, t1, t2, t3
Satisfaction with Life Scale (SWLS, [52,58])	satisfaction with life	t0, t1, t2, t3
Assessments (conducted by SLT, evaluated by independent rater)		
Montgomery–Asberg Depression Scale (MADRS, [39,59])	depression	t0, t1, t2, t3
Mini Mental-State Examination (MMSE, [37,60])	cognitive status	t0, t1, t2, t3
Scenario test (ST, [53,61])	communicative–pragmatic function	t0, t1, t2, t3
Visual Analog Scale (VAS, [55])	mood	before and after the first and fifth individual therapy sessions; before and after the first and fifth group therapy sessions
Interviews (conducted by independent rater with participants and caregiver)		
Semistructured interviews	views and satisfaction with the current therapy; effectiveness of the intervention	after intervention
Checklists (filled out by SLT)		
Fidelity checklist	self-reflection according to adherence to the biographic-narrative approach	after every individual and every group therapy session
Checklists (filled out by independent rater)		
Fidelity checklist	recording of quality and evaluation of adherence in a random sample of 10% of video recordings of all therapy sessions	at the end of the study

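### The success criteria set an uncontrolled pre-post SAQOL-39 test beside the randomised comparison and do not say that only the latter decides efficacy

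*Protocol article*

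**What the plan says.** Section 2.4.5 (Criteria for Success) lists six criteria for phase two:

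1. "Significant improvement in SAQOL-39 score with a medium effect size from pre- to post-intervention".
2. A significantly greater SAQOL-39 improvement from t0 to t1 in the therapy group than in the waiting group.
3. Generally positive perceptions of acceptability in the interviews.
4. Fidelity of at least 80% in the independently rated sample.
5. "Stable values or improvements on the MADRS".
6. The same requirement for the VAS.

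The section does not say whether all, some or any of these must be met, and it does not rank them. It gives no number for a medium effect.

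Other parts of the article bear on this list:
- Table 1 has the SAQOL-39 filled out by participants, and section 2.3.1 says that participants cannot be blinded.
- Table 1 schedules the VAS "before and after the first and fifth individual therapy sessions; before and after the first and fifth group therapy sessions".
- The Discussion says of declining awareness of deficits that "it is conceivable that an improvement in QoL may not (only) be due to the intervention".
- Section 2.3.5 gives one power calculation, a "total sample size of 24 for an estimated effect size of f = 0.275 (d = 0.55; α = 0.05; power = 0.8"), and does not link it to any criterion.

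**The concern.** The trial randomises 24 people to therapy or waiting so that change due to the therapy can be separated from change that would have happened anyway. Criterion 1 does not use that control. It asks only whether an unblinded self-report score rose from before to after the intervention. Declining awareness, other therapies taken at the same time (allowed under section 2.1 and acknowledged in the Discussion) or repeated completion of the questionnaire could each raise it.

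As the list stands, a report could meet criterion 1, miss criterion 2 and still describe the trial as successful.

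The added demand for a medium effect looks like a safeguard, but it is a threshold on a noisy estimate, set close to the planning value of d = 0.55. It does not distinguish a therapy effect from any other gain, and it fails many trials in which the planned effect is real.

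Criteria 5 and 6 also lack a comparator. For the VAS none is possible, because it is measured only around therapy sessions and so gives no values from the untreated waiting period.

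**Working it through.** **Inputs from the article.** N = 24, 12 per arm (section 2.3.4: "the second half (*n* = 12) assigned to the waiting group"); d = 0.55, f = 0.275, α = 0.05, power 0.80 (section 2.3.5).

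**Assumptions, not in the article.** Correlation ρ between time points of 0.5 to 0.8; two-sided tests; 'medium' means observed d ≥ 0.5 in baseline-SD units; criterion 1 pools both arms (n = 24), each before and after its own therapy. Dropout and clustering by therapy group are not modelled; both would lower power.

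**Step 1. The plan's own figure.** Section 2.3.5 says that "an a priori power analysis was conducted using G*Power 3.1.7" but gives neither the test nor ρ. For repeated-measures ANOVA, λ = f²·N·m/(1−ρ).
- m = 3 measurements, ρ = 0.5: λ = 0.0756 × 24 × 3 / 0.5 = 10.89 on 2 and 44 df, power 0.822.
- m = 2, ρ = 0.6: λ = 0.0756 × 24 × 2 / 0.4 = 9.08 on 1 and 22 df, power 0.821.

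So 24 is reproducible, but under more than one reading.

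**Step 2. Criterion 1 with no therapy effect.** In baseline-SD units the SD of change is √(2(1−ρ)): 1.00 at ρ = 0.5 and 0.775 at ρ = 0.7. The noncentrality for a common gain g is g·√24/SD. For g = 0.4 this is 1.96 and 2.53.

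| Non-specific gain (assumed) | Pre-post significant, ρ 0.5 to 0.7 | Significant and observed d ≥ 0.5 |
|---|---|---|
| 0.2 SD | 15% to 23% | about 5% to 8% |
| 0.3 SD | 29% to 44% | about 13% to 17% |
| 0.4 SD | 47% to 68% | about 29% to 32% |

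If both arms share the gain over the same ten weeks, criterion 2 is met in its favourable direction in only 2.5% of trials.

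**Step 3. What the cut-off costs when d = 0.55 is true.** At ρ = 0.5 the noncentrality is 0.55 × √24 = 2.69 and the power for significance is 0.73. Significance needs an observed d of about 2.069/√24 = 0.42, so a threshold of 0.5 binds beyond it. The pass rate falls to 0.59. At ρ = 0.7 it falls from about 0.92 to 0.63, or to 0.84 if d is standardised by the SD of change. If the true effect equals the cut-off, the chance of exceeding it is about 50% at any sample size.

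**Step 4. 'Stable' read as no significant worsening.** With n = 24, a true worsening of 0.2 or 0.3 SD of change still passes in about 85% or 71% of trials. Read instead as a mean that is not worse, a true change of zero passes about half the time.

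**Step 5. Criterion 2.** For a between-arm difference in change of 0.55 SD, the standard error is SD(change) × √(2/12). At ρ = 0.5 this is 0.408, giving noncentrality 1.35 and power 0.25.

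| ρ | Criterion 1 with cut-off | Criterion 2 | Both |
|---|---|---|---|
| 0.5 | 0.59 | 0.25 | 0.23 |
| 0.7 | 0.63 | 0.38 | 0.34 |
| 0.8 | 0.65 | 0.53 | 0.45 |

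If f = 0.275 is instead a group-by-time interaction over two times, the difference in change is 4 × 0.275 = 1.1 SD. Criterion 2 then has power 0.73 (ρ = 0.5), 0.82 (0.6) or 0.91 (0.7), and requiring criterion 1 as well costs almost nothing.

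**The case against.** The list is headed as criteria for success, not for efficacy, and it already contains the controlled comparison as well as acceptability and fidelity. In a progressive disease, stable mood can reasonably be read as a check that the therapy does no harm. The margin for 'stable' is detail that the full protocol or an analysis plan may hold. The Discussion declares the awareness problem as a limitation and plans communicative and cognitive assessments because of it. The cut-off also reduces false passes under a non-specific gain, as the table in step 2 shows. No text supports a gain of a particular size.

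Much of this stands. The no-deterioration reading of criteria 5 and 6 is legitimate, the missing margin is not the point, and the sizes in step 2 are assumptions shown as a range. What remains is that section 2.4.5 gives an uncontrolled test of the primary outcome the same standing as the controlled one. The cut-off reduces false passes only by demanding a larger gain; it does not identify the cause of the gain.

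A reader might also infer that criterion 1, the cut-off and the stability criteria together put the planned 80% out of reach. The article does not support that. It does not say that all criteria are required, and it ties the 80% to no criterion. At a 0.55 SD difference in change, nearly all of the shortfall comes from criterion 2 itself: adding criterion 1 costs about 2 to 8 percentage points. Under the interaction reading, both SAQOL-39 criteria can be met with more than 80% probability.

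**Conclusion.** The point holds as a fault in how success is defined. Only criterion 2 is a controlled test of the primary outcome, and the plan does not say that it decides efficacy. Criterion 1 can be met with no specific effect. How often depends on an assumed non-specific gain and on ρ: from about 15% for significance alone at 0.2 SD and ρ = 0.5 to 68% at 0.4 SD and ρ = 0.7. With the cut-off the range is about 5% to 32%, if 'medium' means an observed d of at least 0.5 in baseline-SD units. Criteria 5 and 6 cannot support an efficacy claim, although they may serve as checks for deterioration.

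The comparison with criterion 2 assumes that the non-specific gain is shared by both arms. A waiting control does not remove a gain that comes from knowing one is in therapy.

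**What to change.** Rewrite the list in section 2.4.5:

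- Name the between-arm SAQOL-39 difference at t1, adjusted for t0, as the only criterion for claiming efficacy.
- Delete the medium-effect requirement and report the estimate with its 95% confidence interval.
- Report pre-post SAQOL-39, MADRS and VAS as supportive results with confidence intervals. For MADRS add the between-arm difference at t1, which the t0 and t1 assessments of all participants already allow.
- Keep acceptability and fidelity as feasibility criteria.

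The cost is one rewritten list and no new data. The downside is that a positive pre-post result alone can no longer be called success.

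The change does not restore 80% power. For a 0.55 SD difference, the comparison of changes has 0.25 to 0.53 (ρ 0.5 to 0.8). Adjusting t1 for t0 replaces the SD of change by √(1−ρ²), that is 0.866 to 0.600. The noncentrality becomes 0.55/(0.866 × 0.408) = 1.56 to 0.55/(0.600 × 0.408) = 2.25, and power on 21 df about 0.32 to 0.57. At ρ = 0.5, 80% for the comparison of changes would need about 52 per arm. The sponsor should therefore also state which effect f = 0.275 refers to.

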Quantitative analysis is performed as both a per-protocol and intention-to-treat analysis to maximise external and internal validity while minimising statistical bias to maximise external and internal validity while minimising statistical bias. Complete drop-outs will be treated differently from missing values (e.g., due to an individual’s absence in individual or group therapy sessions in which a VAS was conducted). In these individual cases, imputation is considered. There are no plans to promote the retention of participants or intentions to follow-up in the case of individuals who drop out or deviate from the intervention protocol. There is no interim analysis planned.

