#### 2.4.6. Assessment and Management of Risk

Both through participation in the focus group interview and through participation in the group therapy sessions, participants might meet other persons with PPA who are more advanced in the course of the disease than they are themselves. This confrontation with other participants’ symptomatology could initially increase awareness of their own disorder. However, most of the research on this topic suggests that persons with PPA generally experience interactions with peers in a positive way [13,65]. Our own clinical experience with previous completed studies supports these findings.

The confrontation with one’s personal history in the biographic-narrative approach can also stimulate negative memories. Nevertheless, Corsten et al. (2015) provided empirical evidence that participants usually find a positive way of dealing with the experience on their own. The SLT will pay attention to spontaneous reactions of the participants, such as meta-linguistic comments, changes in facial expression, increased sighing, or zero reactions. Signs of excessive demands or discomfort will be documented and addressed in individual discussions with the participants concerned. If the deputy study director ([name]) or the clinicians involved ([name], [name]) come to the conclusion that the continuation of the therapy would harm the participants, the therapy will be stopped immediately. There is no audit for the planned study.

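### Participants whose therapy is stopped for harm can be missing from the acceptability and MADRS success criteria, because the follow-up statement conflicts with the rule that everyone is assessed and interviewed

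*Protocol article*

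**What the plan says.** Section 2.4.5 lists six criteria for success of phase two. The third is that, in the semistructured interviews, "the participants report generally positive perceptions about the acceptability of the intervention". The fifth reads "Stable values or improvements on the MADRS". Neither gives a denominator, an analysis set, a time point or a rule for people whose therapy ended early.

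Section 2.4.6 provides that if the deputy study director or the clinicians "come to the conclusion that the continuation of the therapy would harm the participants, the therapy will be stopped immediately". It does not mention later assessments or the interview.

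On what happens afterwards, the article points in two directions:

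- Section 2.4.3: "There are no plans to promote the retention of participants or intentions to follow-up in the case of individuals who drop out or deviate".
- Section 2.4: everyone enrolled in phase two is assessed at four times, ten weeks apart. Table 1 includes the MADRS at each.
- Section 2.4.1: the interviews are held with all participants and their caregivers. Table 1 places them after the intervention and gives their aim as "views and satisfaction with the current therapy; effectiveness of the intervention".
- Section 2.4.3 again: "Quantitative analysis is performed as both a per-protocol and intention-to-treat analysis". It adds that "Complete drop-outs will be treated differently from missing values", without saying how. Imputation is only under consideration, most naturally for single missing values.

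Reasons for drop-out are to be documented descriptively (section 2.4.3) and are not tied to the success criteria.

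**The concern.** A stop for harm is not a random loss. It is triggered by the kind of distress that the acceptability and mood criteria are meant to detect. If such a person is treated as having dropped out or deviated, the follow-up statement means that nobody intends to obtain the later MADRS scores, and the interview may not take place. The two criteria would then be judged on those who tolerated the therapy, and the bias would run towards success.

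This matters here because the approach is newly adapted for PPA. The article itself foresees that the sessions can stir negative memories (section 2.4.6) and cause frustration (Discussion). All 24 participants receive therapy, since the waiting group is treated after ten weeks (section 2.3.3), so all are exposed to a possible stop. Scores and interviews that were never obtained cannot be recovered by a later analysis plan.

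**Working it through.** **Step 1. The passages side by side.**

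| Question | Statement that includes a stopped participant | Statement that can exclude one |
|---|---|---|
| Later MADRS | Section 2.4: all enrolled assessed at t0 to t3 | Section 2.4.3: no intention to follow up those who drop out or deviate |
| Interview | Section 2.4.1: all participants | Table 1: held after the intervention; section 2.4.3 as above |
| Analysis set for the MADRS criterion | Section 2.4.3: intention-to-treat | Section 2.4.3: per-protocol is also named, and neither is said to decide success |

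Someone whose sessions end part-way has, on a natural reading, dropped out or deviated, and section 2.4.3 makes no exception for stops for harm. No passage settles the matter either way. Because MADRS assessments are ten weeks apart, a person stopped between two of them may have scores only from before the worsening.

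**Step 2. Inputs for an illustration.** The denominator comes from section 2.3.4: four groups of six, 4 × 6 = 24. Higher MADRS means more depression (section 2.4.1). The article gives no stopping rate and no expected MADRS change, so these are assumptions:

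- *k* participants are stopped for harm and have no later score.
- The other 24 − *k* improve by *c* points on average.
- The stopped participants worsen by *w* points on average.

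**Step 3. Formulas.** Without the stopped participants, the mean change is −*c*. Over all 24 it is

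[*k*·*w* − (24 − *k*)·*c*] / 24,

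which becomes a worsening once *w* > *c*·(24 − *k*)/*k*.

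**Step 4. Results.**

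| *k* | *w* that must be exceeded, *c* = 1 | *w* that must be exceeded, *c* = 2 | Mean of all 24, *c* = 1, *w* = 10 | Mean of all 24, *c* = 1, *w* = 15 |
|---|---|---|---|---|
| 1 | 23 | 46 | −0.54 | −0.33 |
| 2 | 11 | 22 | −0.08 | +0.33 |
| 3 | 7 | 14 | +0.38 | +1.00 |
| 4 | 5 | 10 | +0.83 | +1.67 |

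Example, *k* = 3, *c* = 1: the threshold is 1 × 21/3 = 7. With *w* = 10 the mean of all 24 is (30 − 21)/24 = +0.38, against −1.00 in those who remain.

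**Step 5. Acceptability.** The third criterion has no rate or threshold, so no size can be derived. Two invented cases bracket it. If all 21 people interviewed are positive and 3 were stopped, the share falls from 100% to 21/24 = 87.5%, which would still be called generally positive. If opinion is nearly even and a simple majority is required, 11/21 = 52.4% passes but 11/24 = 45.8% does not.

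**The case against.** The strongest objection is that the article never says a stopped participant leaves the study. Section 2.4.6 ends the therapy, not the assessments. Section 2.4 has all enrolled participants assessed, section 2.4.1 has all interviewed, and section 2.4.3 names intention-to-treat. Section 2.1 sets out what is done when depressive signs appear during the study, again without removing the person. This stands. A reader might infer that harmed participants necessarily drop out of both criteria; the documents do not support that. They leave it open, and only one of the conflicting statements leads there.

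The size is also hypothetical. One stop would need a worsening above 23 points to reverse a 1-point improvement, and on most readings of generally positive a few stops would not change the acceptability verdict. This stands too.

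A third objection is that analysis sets and the handling of drop-outs belong in an analysis plan that is not shown. This is right for the details, but not for data collection: the lack of intended follow-up is stated here, and intention-to-treat in name does not supply scores that were never taken. The analysis sets named apply to the quantitative analysis, so they do not help the interview criterion.

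Finally, the same conflict touches the SAQOL-39 criteria. That is true. The acceptability and MADRS criteria are singled out because the reason for the stop is most directly what they measure.

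A reader might also want every stop for harm counted as a failure on the MADRS whatever was measured later. That would override observed stable values and is a debatable choice, not a correction.

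**Conclusion.** The point holds as a conflict between statements with a predictable direction of bias. The follow-up statement in section 2.4.3 cannot be squared with assessing and interviewing everyone, or with a meaningful intention-to-treat analysis. If it is applied to people stopped for harm, they can be missing from the third and fifth success criteria, and their absence favours success.

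The size is unknown. If the remaining participants improve by 1 MADRS point on average, 2, 3 or 4 stops with an average unmeasured worsening above 11, 7 or 5 points would reverse the sign of the overall mean. If they improve by 2 points, the thresholds double. For acceptability the effect depends on a threshold that the plan does not set. The illustration rests on stopped participants having no later score, which the plan permits but does not prescribe.

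**What to change.** 1. In section 2.4.3, reconcile the follow-up statement with sections 2.4 and 2.4.1. State that participants who stop therapy stay, with their consent, in the scheduled MADRS assessments and are offered the existing semistructured interview.
2. In section 2.4.5, read the acceptability and MADRS criteria on everyone who started therapy. Use observed MADRS values wherever they exist.
3. Where a person stopped for harm has no later data, treat the outcome as unfavourable at least in a sensitivity analysis. If the MADRS criterion is a mean, assign a range of worsening and report where the conclusion changes. If it is a count of individuals, count the person as not stable. For acceptability, count the person as unfavourable.
4. Report the number of stops for harm beside each of the two criteria.

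The cost is wording in two sections and slightly more assessment work, using instruments and an interviewer already in the plan. The results may look less favourable. The rule on when therapy is stopped is not touched.
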